### Eligibility criteria

(1) Elderly patients aged ≥ 60 years who underwent vertebral augmentation for OVCF and experienced recurrent fractures after the initial surgery; (2) Elderly patients aged ≥ 60 years with bone mineral density T ≤ -2.5.

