**Methods:**

We will collect vertebral and peripheral blood from 500 elderly OVCF patients undergoing surgery, extract DNA, and generate whole genome genotype data and DNA methylation data. Observation indicators will be collected and combined with one-year follow-up data. A healthy control group will be selected from a natural population cohort. Epigenome-wide association studies (EWAS) of osteoporosis and bone mineral density will be conducted. Differential methylation analysis will compare candidate gene methylation patterns in patients with and without refracture. Multi-omics prediction models using genetic variants and DNA methylation sites will be built to predict OVCF risk.

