The objective of this study is to investigate the genetic and epigenetic markers associated with osteoporosis and bone mineral density, and their impact on refracture risk among elderly patients. We aim to collect vertebral body blood and peripheral blood samples from 500 patients with OVCF who will undergo detailed clinical assessments, genome-wide genotype and methylation profiling at baseline. Following the surgical intervention, these patients will be followed up for 1 year to monitor refracture events, during which clinical and genome-wide methylation data will be collected again. These valuable data will enable us to identify genetic and epigenetic markers that can predict OVCF and refracture risk in the elderly and develop accurate prediction models.

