### Sample size

The power of EWAS is essential for detecting differentially methylated positions (DMPs) between cases and controls. Similar to GWAS, the power of EWAS depends on four key factors, including study design, sample size, effect size, and burdon of multiple test correction. Previous simulation analysis has shown that a sample of 500 cases and 500 controls would achieve 80% power to detect differential methylation at epigenome-wide significance (*P* < 1E-6) with a methylation odds ratio of 1.28 or mean methylation differences of 5% in case–control designs of EWAS (cite the original pubication) [19]. Therefore, we aim to recruit 500 elderly patients with OVCF who underwent vertebral augmentation surgery, as well as 500 healthy controls matched for age, gender, and race from the CAS cohort who did not develop OVCF or osteoporosis. This sample size will provide adequate statistical power for detecting significant differences in DNA methylation levels between cases and controls and enable us to identify epigenetic markers associated with refracture after vertebral augmentation surgery for OVCF.

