### Exclusion criteria

(1) Patients with severe cardiovascular and cerebrovascular diseases, including but not limited to myocardial infarction, stroke, and severe arrhythmias; (2) Patients with significant organ failure, such as end-stage renal disease requiring dialysis, or liver failure requiring transplantation; (3) Patients with contraindications to vertebral augmentation surgery, such as coagulopathy or anticoagulant therapy that cannot be safely managed; (4) Patients with skin ulceration, infection, or rash around the puncture point that would increase the risk of complications during surgery; (5) Patients requiring open surgery for their OVCF, as this may indicate a more complex or severe fracture that could affect the study outcomes; (6) Patients who are unable to cooperate with surgery due to cognitive impairment, psychiatric illness, or other reasons that would make the procedure unsafe or unsuccessful; (7) Patients with a history of pathological fractures, indicating underlying bone disease or malignancy.

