### Inclusion criteria for the control group

(1) Diagnosed elderly patients (aged 60 years and older) with OVCF who underwent vertebral augmentation and did not experience refracture within a specified follow-up period after the initial surgery; (2) Elderly patients aged 60 years and older with a bone mineral density T-score of -2.5 or lower, indicating osteoporosis.

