### Biomarker identification and prediction analysis

The GWAS of bone mineral density will be carried out in PLINK using linear regression model, assuming an additive allele effect. Covariates for age, gender, drug usage and the first five principal components to account for residual population structure will be also included in the model. The genomic control inflation factor will be used to adjust the *p*-values. The adjusted *p*-values equal to or smaller than 5E − 8 will be considered as genoome-wide significant. We will conduct a GWAS using case–control design to invesgate the genetic variants associated with osteoporosis.

This study will use whole-genome methylation data from vertebral and peripheral blood samples of 500 osteoporosis patients with recurrent fractures after vertebral augmentation and 1000 natural population controls from the Chinese Academy of Sciences. To identify differentially methylated positions (DMPs) between patients with and with out refracture, we will perform an epigenome-wide association study (EWAS) and meQTL analysis. Patients with refracture who underwent vertebral augmentation will be selected as cases, and an equal number of patients without refracture will be selected as controls based on age range and epidemiological indicators such as BMI, disease, and medication history. We will analyze changes in methylation levels of osteoporosis- and bone mineral density-related sites in elderly patients with refracture within one year after surgery. The R language DMRfinder package will be used for analysis, and functional annotation of the identified DMPs and differentially methylated regions (DMRs) will be performed.

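### Refracture is an entry criterion in one part of the protocol and the one-year outcome in another, and the two control groups are never assigned to their own comparisons

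*Protocol article*

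**What the plan says.** The protocol article describes the 500 patients in two ways.

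- **Refracture as a condition of entry.** Criterion (1) under Eligibility criteria covers patients aged 60 or over "who underwent vertebral augmentation for OVCF and experienced recurrent fractures after the initial surgery". The section Biomarker identification and prediction analysis repeats this, giving the study material as "500 osteoporosis patients with recurrent fractures after vertebral augmentation and 1000 natural population controls".
- **Refracture as an outcome.** The Abstract states: "We will collect vertebral and peripheral blood from 500 elderly OVCF patients undergoing surgery". The Background profiles the patients at baseline and then says that "these patients will be followed up for 1 year to monitor refracture events, during which clinical and genome-wide methylation data will be collected again". The Sample size section recruits 500 operated OVCF patients without mentioning refracture. Recruitment of patients calls the study a prospective cohort.

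Controls also appear in two forms. The Sample size section plans "500 healthy controls matched for age, gender, and race from the CAS cohort who did not develop OVCF or osteoporosis". Inclusion criteria for the control group describes OVCF patients "who underwent vertebral augmentation and did not experience refracture within a specified follow-up period after the initial surgery", and lists a T-score at or below −2.5. The number of population controls is 500 in the Sample size section and 1000 in the analysis section and in Advanced features of this study.

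**The concern.** The same 500 people cannot be enrolled around surgery with their outcome unknown and also be selected because they refractured. The wording appears in both the eligibility and the analysis sections, so it is not one slip of the pen.

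If the eligibility text governs, every enrolled case has had the event. The proportion who refracture and the risk given baseline methylation then cannot be estimated. Blood may also be drawn after the refracture, so a methylation difference could be a consequence of the fracture or its treatment. That matters for a study whose title claims causal impact and a prospective cohort.

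The control groups raise a related problem. A healthy person without OVCF or osteoporosis can inform the osteoporosis comparison but cannot serve as the non-refractured comparator among operated patients. The Sample size section nevertheless ends by saying that its 500-versus-500 calculation also allows refracture markers to be found.

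**Working it through.** **Step 1. The sections side by side**

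| Section | Who the 500 are | Role of refracture |
|---|---|---|
| Abstract, Methods | OVCF patients having surgery | compared later, with versus without |
| Background, objective | OVCF patients profiled at baseline | outcome over one year |
| Sample size | operated OVCF patients | no requirement |
| Eligibility criteria (1) | operated patients who refractured | entry condition |
| Biomarker identification | patients with recurrent fractures | true of all 500 |

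Under the last two rows, 0 of the 500 are free of refracture. The 500 cases plus 500 healthy controls of the Sample size section then contain no non-refractured OVCF patients. The 1:1 refracture comparison in the analysis section would need them in addition.

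**Step 2. Expected refractures in a cohort of 500**

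Input: the 6.2% to 51.8% literature range in the Background. No time horizon is given; applying it at one year, without dropout, is an assumption.

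- 500 × 0.062 = 31
- 500 × 0.518 = 259

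Conversely, observing 500 refractures prospectively would need 500/0.518 = 965.3, so 966 patients, up to 500/0.062 = 8,065. This converse applies only if refractures are to arise during follow-up.

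**Step 3. What the stated power covers**

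The article takes 80% power for 500 versus 500 at P < 1E-6 and a 5% mean difference from a cited simulation. It gives no SD, so the figure cannot be reproduced independently. With a two-sided normal approximation:

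- z-sum = 4.892 + 0.842 = 5.733
- standardised difference = 5.733 × √(2/500) = 0.363
- implied SD = 0.05/0.363 = 0.138

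The 80% is attainable with that SD and is not disputed. An SD of 0.10 would give 99.9%, and 0.15 would give 65%.

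**Step 4. The same calibration for the refracture comparison**

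For m cases and m controls, treated as independent groups:

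- power = Φ(5.733 × √(m/500) − 4.892)
- difference detectable with 80% power = 5 points × √(500/m)

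| m per group | Power for 5 points | Detectable difference |
|---|---|---|
| 31 | 0.03% | 20.1 points |
| 100 | 1% | 11.2 points |
| 200 | 10% | 7.9 points |
| 250 (the most 500 patients allow) | 20% | 7.1 points |

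At 51.8% only 500 − 259 = 241 patients are without refracture, so 1:1 selection gives 241 per group and 18% power. Using every non-refractured patient as a control gives about 0.2% power at the 6.2% rate and 20% at the 51.8% rate.

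**The case against.** The best defence reads the eligibility and control-group sections as the two arms of a refracture case-control comparison, with healthy controls kept for the osteoporosis EWAS. Much of this stands. Recruitment of patients and Inclusion criteria for the control group both admit non-refractured patients, and the Abstract and the analysis section show two distinct comparisons. Three stronger conclusions that a reader might draw are therefore not supported.

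- *The study cannot address refracture at all.* A retrospective contrast between refractured and non-refractured patients could still be formed. What is lost is incidence, prospective risk and assurance that methylation preceded the event.
- *One control group is defined in two incompatible ways.* The definitions exclude each other, but they fit two groups for two comparisons. The fault is that no section separates or assigns them.
- *Unequal exclusions build comorbidity imbalance into the refracture contrast.* The item "Patients with severe cardiovascular and cerebrovascular diseases, including but not limited to myocardial infarction, stroke, and severe arrhythmias" stands under a heading that names no arm, so its restriction to refractured patients is only inferred from the order of sections. The analysis section also selects non-refractured controls on disease and medication history.

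The defence does not remove the core contradiction. No section states the two-arm reading, and under it the eligibility of the whole cohort is never given. The analysis section still makes all 500 refractured, and the Sample size section still attaches the healthy-control calculation to refracture markers. Nor is this detail that an article leaves to a fuller document, because the article states conflicting populations.

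Joining criteria (1) and (2) by *or* would not help. It would admit patients without refracture, but also osteoporotic people with no OVCF or surgery, and it would still conflict with the analysis section.

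**Conclusion.** The contradiction over the role of refracture is established by the text alone and must be resolved. The eligibility wording, if followed, leaves only a retrospective case-control contrast. The controls are a lesser fault of assignment: two groups not tied to their comparisons, 500 versus 1000 not reconciled, and a power statement stretched to a comparison it does not cover.

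On size, a cohort of 500 operated patients would give about 31 to 259 refractures, assuming that the literature range holds at one year without dropout. If the article's 80% is accepted and the same variability applies, power for the planned 5-point difference among refracture cases is about 20% at best. These figures rest on a two-sided test and an SD back-solved from the article's own statement. The contradiction does not depend on them.

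**What to change.** - **Eligibility criteria:** remove refracture from cohort entry and make it the one-year outcome. State whether criteria (1) and (2), here and in the control section, are joined by *and* or *or*, and so whether the T-score criterion applies to everyone.
- **Non-refracture comparators:** define them as cohort members without refracture in that year, replacing the unspecified follow-up period, under the same exclusions as the rest of the OVCF cohort.
- **CAS controls:** give them their own heading, assign them to the osteoporosis EWAS, and reconcile 500 with 1000. The surgical exclusions should not carry over to them.
- **Biomarker identification:** describe the material as 500 operated OVCF patients.
- **Sample size:** limit the 80% claim to cases versus healthy controls, and state what the expected number of refractures can detect.
- **Timing:** reconcile the Abstract (patients having surgery), the Background (baseline before follow-up) and Recruitment of patients (after augmentation). Leave anyone enrolled after refracture out of the prospective refracture analysis.

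Most of this is wording and needs no new procedures. The real costs are fewer refracture cases and a less favourable stated power for that EWAS. Recruitment was scheduled to end in December 2023 and the article appeared in June 2024. If the eligibility text was applied as written, rewording cannot restore a prospective cohort, and the refracture comparison would have to be reported as retrospective.

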## Methods

### Recruitment of patients

This will be a prospective multicenter cohort study conducted in 5 medical centers, including Peking University International Hospital, Beijing Tiantan Hospital affiliated to Capital Medical University, Beijing Changping District Hospital, Tengzhou Central People’s Hospital, and Linfen People’s Hospital. The study was approved by the Biomedical Ethics Committee of Peking University International Hospital (batch number: 2022-KY-0010-01). Recruitment of elderly patients with OVCF after vertebral augmentation and those without refracture will take place from December 2022 to December 2023. All participants will provide informed consent. The flow chart is presented in Fig. 1. An example of refracture in elderly individuals with osteoporosis who undergo vertebral augmentation is shown in Fig. 2.

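### The protocol contradicts itself on whether refracture is an entry criterion or a one-year outcome, which leaves the timing of case methylation relative to the event unsettled

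*Protocol article*

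**What the plan says.** All references are to the protocol article.

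**Refracture as a condition of entry**
- Eligibility criteria: the first criterion covers patients aged 60 or over "who underwent vertebral augmentation for OVCF and experienced recurrent fractures after the initial surgery".
- Inclusion criteria for the control group: comparators are operated patients who "did not experience refracture within a specified follow-up period after the initial surgery". The length of that period is not given.
- Recruitment of patients: "Recruitment of elderly patients with OVCF after vertebral augmentation and those without refracture will take place from December 2022 to December 2023".
- Biomarker identification and prediction analysis: the methylation data come from "500 osteoporosis patients with recurrent fractures after vertebral augmentation and 1000 natural population controls".

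**Refracture as a follow-up outcome**
- Abstract, Methods: vertebral and peripheral blood is taken from 500 OVCF patients having surgery, and one-year follow-up data are then added.
- Background, objective: the 500 patients are genotyped and methylation-profiled at baseline. "Following the surgical intervention, these patients will be followed up for 1 year to monitor refracture events". The stated purpose is to find markers that predict OVCF and refracture.
- Sample size: "we aim to recruit 500 elderly patients with OVCF who underwent vertebral augmentation surgery", with no requirement of refracture.
- Exclusion criteria: several concern fitness for augmentation, so they presuppose an operation still to come.
- Table 1: assessments are scheduled before the operation and one year after it.

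**The concern.** Whether refracture comes before or after the blood draw decides what the refracture methylation scan can show. Methylation can change with a new fracture, immobility, further surgery or altered treatment. If cases become eligible only once they have refractured, their enrolment sample follows the event, and a difference from non-refractured patients may be an effect of refracture. Such a site marks having refractured; it is not evidence that the site predicts refracture, which is what the objective promises. A larger sample does not help, because it detects consequences as readily as predictors.

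The contradiction also affects the numbers. The Sample size section says its 500 v 500 calculation will serve to identify markers of refracture. That requires about 500 refracture cases, which a cohort of 500 operated patients cannot yield.

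**Working it through.** **1. The passages side by side**

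| Question | Eligibility, control criteria, recruitment and analysis text | Abstract, objective, sample size and Table 1 |
|---|---|---|
| Who are the 500? | Patients who have refractured (Eligibility criteria; analysis section) | Operated OVCF patients |
| When is refracture known? | At enrolment | During the year after surgery |
| How are comparators defined? | By a refracture-free period already observed | By absence of the event in follow-up |
| When is first blood drawn? | No date given; follows the event if drawn at enrolment | At surgery, as baseline |

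The columns cannot both be true of the same 500 people.

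**2. Can 500 refracture cases come from 500 operated patients?**

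Input: the Background cites refracture rates of 6.2% to 51.8%. I apply these as one-year rates with no dropout, which is an assumption.

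- Expected refractures: 500 × 0.062 = 31; 500 × 0.518 = 259.
- Patients needed for 500 refractures: 500 / 0.518 = 965.3, so 966; 500 / 0.062 = 8,064.5, so 8,065.

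The 500 refracture cases in the analysis section are out of reach of the prospective cohort at any cited rate.

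**3. The plan's own power figure**

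The Sample size section gives 80% power with 500 v 500 at P < 1E-6 for a 5% mean methylation difference, citing a simulation. It gives no SD, so the figure cannot be reproduced independently. Using a two-sided normal approximation and solving backwards:

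- SD = 0.05 / [(4.892 + 0.842) × √(2/500)] = 0.138.
- Check: 0.05 / [0.1379 × √(2/500)] − 4.892 = 5.733 − 4.892 ≈ 0.842, and Φ(0.842) = 80%.

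**4. The same formula applied to the refracture scan**

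The analysis section matches 1:1: "an equal number of patients without refracture will be selected as controls". The number of pairs is therefore the smaller of the two groups, and power = Φ{0.05 / [SD × √(2/n)] − 4.892}. At SD 0.138:

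| Refracture rate | Pairs n | Argument of Φ | Power |
|---|---|---|---|
| 6.2% | 31 | 1.428 − 4.892 = −3.464 | 0.03% |
| 50% | 250 | 4.054 − 4.892 = −0.838 | 20% |
| 51.8% | 241 (500 − 259 without refracture) | 3.980 − 4.892 = −0.911 | 18% |

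The maximum is at 250 pairs. Using every non-refractured patient as a control gives 0.17% to about 20%.

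**5. Sensitivity to the SD**

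| Assumed SD | 500 v 500 | 31 pairs | 250 pairs |
|---|---|---|---|
| 0.10 | 99.9% | 0.17% | 76% |
| 0.12 | 95.5% | 0.06% | 41% |
| 0.138 | 80% | 0.03% | 20% |
| 0.15 | 64.8% | 0.02% | 12% |
| 0.20 | 17.4% | 0.005% | 1.8% |

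The absolute values move a great deal with the SD. In every row the refracture scan has less power than the 500 v 500 comparison. Only the 0.138 row agrees with the 80% that the article states.

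**The case against.** The strongest reply is that the design is prospective and only the wording is poor. The Abstract and objective place sampling at surgery, Table 1 has pre-operative and one-year columns, and the exclusions fit pre-operative screening. The analysis section speaks of selecting refractured cases and an equal number without refracture, which suits a nested case-control selection after follow-up. On that view the two sets of inclusion criteria are group definitions under the wrong heading, and the recruitment sentence is too garbled to prove anything.

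Much of this stands. A reader might infer from the eligibility text that every case sample post-dates the refracture, or that the scan cannot find predictors. The article does not support either as fact. The eligibility and analysis sections say who the patients are, not when they were bled; the only stated collection point is surgery, with profiling at baseline. No later operation for cases is described.

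The reply does not remove the contradiction. The clause sits under Eligibility criteria, the operative rule for enrolment. The analysis section separately gives all 500 patients a recurrent fracture, and a nested reading of 500 operated patients cannot produce that number.

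The scope is also limited. Germline genotype does not change with sampling time. The sized comparison (OVCF v healthy) and the specified prediction models (bone mineral density and OVCF risk) do not take refracture as their outcome.

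**Conclusion.** The point holds as an unresolved internal contradiction that must be corrected. It is not a demonstration that samples were taken after the event. Conditional on the eligibility rule being followed, enrolment methylation in refracture cases would follow the outcome and could not support the predictive aim. Conditional on the prospective reading, time order is sound, but the cohort yields about 31 to 259 refractures, and the Sample size section's claim about refracture markers fails: about 0.03% to 20% power with 1:1 matching, against the 80% quoted for 500 v 500.

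The contradiction rests on the text alone. The case counts assume that the cited refracture rates apply over one year without dropout. The power figures further assume the back-solved SD of about 0.138, a two-sided test and a normal approximation on the methylation proportion scale, although the article converts beta values to M values.

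**What to change.** 1. **Cohort.** Define one cohort of OVCF patients enrolled and bled at the index augmentation. In Eligibility criteria, delete prior refracture as a condition of entry.
2. **Outcome.** Move refracture yes/no, from both sets of inclusion criteria, to the outcome definition and the nested case-control definition.
3. **Recruitment of patients.** Reword the recruitment sentence so that it describes enrolment at surgery, without reference to refracture status.
4. **Analysis section.** Describe the 500 as operated OVCF patients, where the text now reads "vertebral and peripheral blood samples of 500 osteoporosis patients with recurrent fractures after vertebral augmentation".
5. **Sampling rule.** State that the refracture methylation scan uses only samples drawn before the refracture. Check sampling dates against event dates, and flag and report separately any patient enrolled after a refracture. This matters in practice because the stated recruitment window closed in December 2023.
6. **Sample size.** Limit the 80% power statement to the 500 v 500 OVCF-versus-healthy comparison. Give the refracture scan its own expected case count and power.

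The work is rewording, a date check and one restated power paragraph. The real cost is scientific: fewer refracture cases, and a much less favourable stated power for that scan.
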